### Mid-intervention (day 30 and 60)

After 1 and 2 months of therapy, the patient will be referred for re-evaluation of the visual outcome measures.

### Post-intervention (day 90)

After 3 months of treatment, the patient will be referred for reassessment of the same visual outcome measures, in addition to measures of compliance, satisfaction, acceptance and adverse reactions to therapy. Patient compliance with the NEIVATECH system will be determined by the number of sessions attended by each patient during the 3 months of the study, while compliance with the patch will be assessed by means of an adherence record to be completed by parents or legal guardians. Patient satisfaction and acceptance to the new therapy will be assessed using the User Satisfaction Evaluation Questionnaire (USEQ) [41] and the Technology Acceptance Model (TAM) questionnaire [42]. Finally, adverse reactions to therapy will be assessed using the standard and pediatric versions of the Simulator Sickness Questionnaire (SSQ) [43, 44], depending on whether the patients are older or younger than 12 years of age.

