**Methods:**

We aim to recruit a total of 60 children with anisometropic amblyopia aged 5-17 years with no previous treatment for amblyopia other than refractive correction from the pediatric ophthalmology units of the University Clinical Hospital of Valladolid and the Vithas Medimar International Hospital of Alicante. Children who meet the eligibility criteria and consent to participate will be randomly assigned to a three-month intervention group of 18 half-hour in-office therapy sessions with the NEIVATECH system (group A) or to a parallel group receiving 2 hours of conventional patching per day at home for the same period of time (group B). Assessments of visual function will be carried out before the intervention and at 1, 2 and 3 months, with changes in distance BCVA being the primary outcome measure to be considered. Patient safety, compliance, satisfaction and acceptance to treatment will also be assessed after therapy as other valuable outcome measures. In addition, a rsfMRI scan will be performed on a subgroup of 5 patients from each group at the pre-intervention visit and at the post-intervention visit to test the effects of both therapies on neural plasticity in the visual cortex.

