## Methods

### Hypothesis and aims

We hypothesise that 9 hours of therapy with the NEIVATECH system, which combines dichoptic training with perceptual learning tasks and gamified elements in an immersive virtual reality (VR) environment, will provide greater improvements in visual function in children with anisometropic amblyopia than conventional patching.

To test our hypothesis, we intend to conduct a small-scale RCT in which 60 anisometropic amblyopic children aged 5-17 years with no history of treatment for amblyopia other than refractive correction alone will be randomly assigned to receive 18 half-hour active vision therapy sessions with the NEIVATECH system over a period of 3 months (group A) or 2 hours of daily patching at home for the same period of time (group B).

The primary outcome measure to be considered will be changes in distance BCVA before and after therapy. Secondary outcome measures will include near BCVA, CSF, binocular vision, stereopsis, fusional vergence, near convergence point and accommodative facility. Other valuable outcome measures to consider after the intervention will be satisfaction, adherence, acceptance and safety of the therapy. In addition, resting-state fMRI (rsfMRI) will also be performed on a subgroup of 5 patients from each group at the pre- and post-intervention visit to provide a rational explanation for the visual improvements obtained with the NEIVATECH system, if any.

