### Sampling

Consecutive sampling of all patients attending the pediatric ophthalmology units of the hospital centres planned for recruitment who met the eligibility criteria will be carried out over a period of 12 months (May 2022 to April 2022). The contact details of all patients who consent to participate will be registered in order that they can be contacted to arrange in-office active vision therapy sessions and scheduled visits. Participants will be assigned to the experimental or control group by block randomization using a computer-generated list of random numbers in order to ensure equal treatment allocation. Once randomized, each patient recruited in Valladolid will also be offered the possibility of participating in the rsfMRI study until the proposed number in each group is reached.

Sample size estimation for this study was carried out using the GRANMO online platform (https://www.imim.es/ofertadeserveis/software-public/granmo/), establishing a minimum distance BCVA difference to be detected in both groups before and after the intervention of 0.15 logMAR, a follow-up loss of 10% and a common standard deviation (SD) of 0.195 logMAR. According to this, a sample size of 30 patients per group would be required, considering an alpha error of 0.05 and a statistical power of 80%. This result is consistent with the sample size used in previous studies in this area [36–38].

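### Satisfaction with and acceptance of the VR therapy are asked only at day 90, so early leavers may go unheard; the patching record is also more exposed to dropout than VR attendance

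*Protocol article*

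**What the plan says.** The abstract of the protocol article names these outcomes and their timing: "Patient safety, compliance, satisfaction and acceptance to treatment will also be assessed after therapy as other valuable outcome measures". The section Hypothesis and aims agrees: "Other valuable outcome measures to consider after the intervention will be satisfaction, adherence, acceptance and safety of the therapy".

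The visit schedule matches. Under Mid-intervention (day 30 and 60): "After 1 and 2 months of therapy, the patient will be referred for re-evaluation of the visual outcome measures". Under Post-intervention (day 90), the visual measures are repeated "in addition to measures of compliance, satisfaction, acceptance and adverse reactions to therapy". The later Follow-up section, six months on, again names visual measures only.

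The day-90 section also defines the instruments:
- VR compliance is "determined by the number of sessions attended by each patient during the 3 months of the study".
- For the other arm, "compliance with the patch will be assessed by means of an adherence record to be completed by parents or legal guardians". How often parents make entries, and when the record is handed in, is not stated.
- USEQ and TAM are assigned to the new therapy, so they concern the VR arm. No satisfaction instrument is named for patching.

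Under Study design, a child may leave at any time by contacting the principal investigator and signing a waiver; no assessment at that moment is mentioned. The Sampling section allows for "a follow-up loss of 10" per cent.

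**The concern.** A questionnaire about liking and accepting a therapy is most informative in the children who reject it. If it is given only at the end, a VR child who leaves because the therapy is disliked is never asked, and no later analysis can recover the answer. The schedule in Study overview sharpens this: 10 of the 18 VR sessions fall in the first month, so more than half of the exposure precedes a day-30 visit that does not include the questionnaires.

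Compliance raises a related but separate issue. An attendance count exists for every VR child, including one who stops in week 3. A parent record has to be obtained from the family. If it is looked at only at day 90, a patching family that does not come back may leave no data. Loss of that kind would tend to remove poor compliers from one arm's figure and not from the other's. This matters because non-compliance with patching is part of the rationale in the Background, and the Discussion says game elements were added to raise compliance.

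**Working it through.** **1. The plan's own sample size.** Inputs from Sampling: difference 0.15 logMAR, SD 0.195 logMAR, alpha 0.05 (two-sided), power 80%, loss 10%.

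n per group = 2 × [0.195 × (1.960 + 0.842) / 0.15]² = 26.53, rounded up to 27. With 10% loss, 27 / 0.90 = 30. The stated 30 per group reproduces, and nothing below alters it. The plan therefore expects about 0.10 × 30 = 3 children per arm to be lost and 27 to be seen at day 90.

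**2. What each measure needs in order to exist for a leaver.**

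| Measure | Arm | Source | Needs day 90, as scheduled? |
|---|---|---|---|
| Compliance | VR | count of sessions attended | no |
| Compliance | Patching | parent adherence record | assessed then; time of return not stated |
| USEQ, TAM | VR | questionnaire to the child | yes |

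**3. Bounds for VR satisfaction or acceptance.** Let p be the favourable rate among attenders and d the number lost out of 30. The article defines no favourable/unfavourable cut-off, so one is assumed here.

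- All leavers unfavourable: p × (30 − d) / 30
- All leavers favourable: [p × (30 − d) + d] / 30

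With d = 3 the lower bound is 0.9p, so the reported rate can be too high by at most one tenth of itself. The values of p, and the losses above 3, are assumptions.

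| Lost (d) | Attenders' rate (p) | Range for all 30 |
|---|---|---|
| 3 (planned) | 80% | 72% to 82% |
| 3 (planned) | 90% | 81% to 91% |
| 6 | 80% | 64% to 84% |
| 9 | 80% | 56% to 86% |

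**4. Patching compliance, if leavers' records were lost.** Let c be mean compliance among attenders and a the mean among leavers. The mean for all 30 is (27c + 3a) / 30, so the reported mean is too high by 0.1 × (c − a). Assuming c = 70% and a = 0% to 30%:

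- a = 0%: (27 × 70 + 3 × 0) / 30 = 63%, an excess of 7 points
- a = 30%: (27 × 70 + 3 × 30) / 30 = 66%, an excess of 4 points

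This excess arises only if the records are in fact not recovered. The VR attendance count has no counterpart to it.

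**The case against.** The strongest reply concerns patching. A reader might infer that patching compliance is collected only at day 90, and that the comparison therefore sets all randomised VR children against patching completers. The article says neither. A record completed by parents may be kept throughout the three months, and a partial one could be retrieved, for instance when the waiver is signed. No analysis set for compliance is defined and no leaver is excluded; such rules are commonly left to the full protocol or SAP. That objection stands: the patching limb is a risk of loss, not a stated exclusion.

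Three further points also stand. Stopping treatment is not the same as being lost: a child who gives up may still attend day 90 and be recorded. USEQ and TAM concern the new therapy only, so a between-arm imbalance cannot arise for satisfaction or acceptance. The rates used in the illustrations are assumed.

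It can also be said that assessment after therapy is the declared intent, and that a day-30 answer measures early opinion rather than final opinion. That is a reason to keep day 90 and report day 30 separately. It does not help the child who leaves before day 90. Nor does the limitation disclosed in the Discussion, that patching cannot be confirmed objectively: it concerns the accuracy of the record, not its unequal exposure to dropout.

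**Conclusion.** The point holds for the timing of USEQ and TAM. The article gives a positive schedule, not mere silence: these measures are what day 90 adds, and the earlier visits are limited to vision. VR acceptability will therefore describe attenders. At the planned 3 of 30 lost, the overstatement is at most one tenth of the reported rate, reached only if every leaver was dissatisfied; with heavier loss it grows. For compliance, the supported statement is that the two arms' measures are unequally exposed to dropout. On the assumed rates the effect would be 4 to 7 points if records were lost; the documents do not show that they will be.

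These are outcomes ranked below the primary and secondary ones. The primary outcome and the sample size are untouched. This is a cheap improvement, to be made before data collection because missing answers cannot be created later.

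**What to change.** - Give USEQ and TAM to the VR arm at the existing day-30 visit and at withdrawal (when the waiver is signed), as well as at day 90. Keep day 90 as the main time point and report day 30 separately.
- Copy the patch adherence record at the day-30, day-60 and day-90 visits and at withdrawal.
- Report compliance, satisfaction and acceptance with the number of leavers per arm beside each figure.
- Show a bound that counts leavers as non-compliant or not satisfied as a sensitivity analysis only. As the main analysis it would misclassify children who leave for other reasons, such as the travel burden noted in the Discussion, or who go on patching outside the study.

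The cost is a few minutes at visits that already take place, a short wording change, and possibly a less favourable acceptability figure.

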## Abstract

**Background:**

Interest in developing alternative methods for the treatment of amblyopia has long been a topic of interest among clinicians and researchers, as prescribed occlusion and penalization therapies do not always provide an effective response and are associated with a high risk of recurrence and non-compliance. Here, we present the protocol of a small-scale RCT to evaluate the safety and clinical efficacy of a novel VR-based system designed to provide binocular vision training to children with anisometropic amblyopia.

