### Study overview

Participation in this RCT will essentially involve five visits (screening, pre-intervention visit, one-month visit, two-month visit and post-intervention visit), in addition to the visits that patients assigned to group A will have to make to carry out the active vision therapy sessions with the NEIVATECH system. These sessions will be 18 in total, will have an average duration of half an hour and will be distributed as follows: five sessions in the first week (Monday to Friday), three sessions in the second week (Monday, Wednesday and Friday) and a maintenance session in the following weeks (on Wednesdays). This is because it has been shown that most of the improvement obtained with visual training in amblyopia occurs during the first weeks of treatment [39–41]. Thus, patients assigned to group A will have to perform 10 sessions of active vision therapy with the NEIVATECH system during the first month of treatment, 4 during the second month and 4 during the third month. On the other hand, patients assigned to group B will have to comply with 2 hours of daily patching during the 3 months of the study.

In addition, a subgroup of 5 patients from group A and 5 patients from group B will have to make two additional visits to the LTI of the University of Valladolid before and after the intervention for a rsfMRI scan (Fig. 3).

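### VR safety is a stated aim, but adverse reactions are scheduled for assessment only once, at day 90, after front-loaded exposure and with nothing described for children who leave early

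*Protocol article*

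**What the plan says.** The Abstract (Background) names safety beside efficacy as the purpose of the trial: "evaluate the safety and clinical efficacy of a novel VR-based system". Two places put the assessment at the end. The Abstract (Methods) says "Patient safety, compliance, satisfaction and acceptance to treatment will also be assessed after therapy as other valuable outcome measures", and Hypothesis and aims says "Other valuable outcome measures to consider after the intervention will be satisfaction, adherence, acceptance and safety of the therapy".

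The visit sections agree with this. Pre-intervention (day 0) lists an eye examination and no symptom questionnaire. For days 30 and 60 the text is: "After 1 and 2 months of therapy, the patient will be referred for re-evaluation of the visual outcome measures". Post-intervention (day 90) adds that "adverse reactions to therapy will be assessed using the standard and pediatric versions of the Simulator Sickness Questionnaire (SSQ"), with the version chosen by whether the child is older or younger than 12. The later follow-up returns to visual measures only.

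The Study overview gives the VR timetable: "five sessions in the first week (Monday to Friday), three sessions in the second week (Monday, Wednesday and Friday"), then one maintenance session a week, 18 in all. Under Study design, a child may leave at any time by contacting the investigator and signing a form. No assessment at that point is described.

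**The concern.** Symptoms provoked by a headset session would be expected close to that session, and most often when sessions are most frequent. The schedule measures far from both. The questionnaire comes at a hospital visit, whereas Study setting places the VR sessions in university rooms, so as described it is not tied to any exposure. With no score from before the first session, a symptom reported at day 90 cannot be separated from one the child already had. A child who stopped because of discomfort in the first weeks contributes no score.

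At stake is the safety statement the trial is meant to support. A low day 90 score could mean that the system is well tolerated, that early symptoms had passed, or that the affected children had left. The data described cannot tell these apart. Acute symptoms that were not recorded near the session cannot be recovered later by analysis.

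**Working it through.** **1. The plan's own session count (Study overview).** 5 in week 1 + 3 in week 2 = 8. The remaining 18 − 8 = 10 sessions at one a week take 10 weeks, so therapy spans 12 weeks. By month, 10 + 4 + 4 = 18. The two descriptions agree.

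**2. Exposure completed before the only safety assessment.**
- Weeks 1 and 2: 8/18 = 44%
- Month 1: 10/18 = 56%
- Months 1 and 2: (10 + 4)/18 = 14/18 = 78%

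Average intensity is 8/2 = 4 sessions a week in weeks 1 and 2, and 1 a week afterwards.

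**3. Distance from the intensive phase to the measurement.** Assume that sessions start at about day 0. Week 2 then ends by day 14, and 90 − 14 = 76 days, about 11 weeks, before the questionnaire. Twelve weeks end at day 84, so day 90 would come about 90 − 84 = 6 days after the end of the last therapy week. A later start shortens both gaps but does not change the order.

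**4. Children expected to have no day 90 score.** The Sampling section gives a difference of 0.15 logMAR, SD 0.195, alpha 0.05 (taken as two-sided), power 80% and 10% loss. Then n = 2 × (1.96 + 0.84)² × 0.195² / 0.15² = 26.5, rounded up to 27 per group, and 27/0.9 = 30. The stated 30 per group reproduces. The plan therefore allows for 30 × 0.10 = 3 children per arm not reaching the end. The documents do not say why they would be lost.

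**5. Visits side by side, as described.**

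| Time | Visual measures | Adverse reactions |
|---|---|---|
| Day 0 | yes | none described |
| VR sessions (18) | – | none described |
| Day 30, day 60 | yes | none described |
| Day 90 | yes | SSQ |
| Early exit | none described | none described |
| Six months after day 90 | yes | none described |

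The three statements on timing (Abstract, Hypothesis and aims, Post-intervention) are consistent with one another. The single time point is thus a stated choice and not an artefact of one loosely worded sentence.

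**The case against.** The strongest reply is that this is a condensed article. Spontaneous adverse-event reporting, a baseline questionnaire or an exit form may be in the full protocol. That stands as a limit on wording: the supportable statement is that these things are not captured by the assessment described. It does not remove the point, because the article assigns the safety assessment to the end of therapy in three places and gives other content to the other visits. Nor does withdrawal go unseen, since sessions attended are counted and leavers sign a form. What is not described is recording why they left.

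Safety is also neither a primary nor a secondary outcome, which limits the weight of the point.

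Several stronger readings are tempting and are not supported:
- **Patching harms are missed, or the arms share no safety measure.** Monocular and binocular acuity, binocular vision and stereopsis are measured in both arms at day 0 and at days 30, 60 and 90. Loss in the patched eye would be visible; it is only not labelled as a safety outcome.
- **The questionnaire is restricted to the VR arm.** The Post-intervention section does not say so, and the questionnaire's items are not in the document.
- **The plan fails to compare safety between arms.** It promises no such comparison; the aim concerns the VR system.
- **Scores from the two versions are pooled.** Nothing says so, and the statistical analysis plan can settle it.
- **A worst case of 0/27 hiding a true 3/30.** This needs every loss to be due to sickness and no completer to have symptoms, and neither has support in the document. No yes/no sickness rate is defined either, and the one-sided 95% upper limit, 1 − 0.05^(1/27) = 10.5%, would still include 10%.

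**Conclusion.** The point holds in a limited form. Followed as described, the stated safety aim rests on one late score from children who reach day 90, taken after 56% of sessions were delivered in the first month and 44% in the first two weeks. There is no pre-exposure value, no link to a session and no assessment on early exit. About 3 of 30 group A children could have no score if the planned 10% loss occurs.

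The direction is towards under-recording of acute early symptoms and of withdrawal caused by them. The size cannot be given, because the document contains no rate of sickness and no reasons for loss. The conclusion assumes that the article's visit descriptions are complete as to safety assessment. It does not touch the primary outcome or the sample size. It is a worthwhile, inexpensive improvement, not a fatal fault.

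One small wording gap belongs with it: the age rule for the questionnaire version does not cover a child aged exactly 12.

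**What to change.** **Group A.** Give the age-appropriate SSQ before and immediately after the first session, and again after a late session of the intensive phase, for example the last session of week 2. Keep the day 90 administration. Obtain the SSQ and the reason for stopping from any child who leaves early.

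**Both arms.** Ask about adverse events at the existing day 30, 60 and 90 visits. Report the fellow-eye BCVA, which is already measured, as a safety outcome as well.

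**Wording.** State which SSQ version a child aged exactly 12 receives.

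**Cost.** Three added questionnaires per group A child, at most 3 × 30 = 90 in all, plus one for each early leaver. Each takes a few minutes at a session that already takes place. The adverse-event question at existing visits adds some data entry. No extra patients and no extra scheduled visits are needed.

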### Follow-up

Six months after the post-intervention visit, patients will be seen at the recruiting centres’ pediatric ophthalmology units according to daily clinical practice for reassessment of the visual outcome measures considered in the study.

### Data analyses plan

A professional biostatistician has been consulted to design the data analysis plan for the study, in which descriptive analysis of all data will be provided, including means and SDs or medians for continuous variables and proportions for categorical variables.

Variables will be analyzed to assess distribution/normality (Kurtosis and Skewness) and by histogram analysis to establish whether they will be analyzed with parametric or non-parametric tests. On the one hand, parametric data will be analyzed using the unpaired T-test, Analysis of Variance (ANOVA) for comparison between groups and multiple linear regression to predict values according to the variables of interest. On the other hand, non-parametric data will be analyzed using the Mann-Whitney U test or the Chi-squared test, the Kruskal-Wallis H test and other non-parametric methods.

For the purposes of the rsfMRI study, analyses of grey matter, white matter diffusion and functional connectivity will be performed. To quantify the variation between the metrics obtained in the two acquisitions (pre-intervention and post-intervention), a coefficient of variation of (Mt_0_ − Mt_1_ / Mt_0_) × 100 will be used, where M will be the metric considered, t_0_ will correspond to the first acquisition (pre-intervention visit) and t_1_ will correspond to the second acquisition (post-intervention visit).

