## Background

Amblyopia has traditionally been defined as a reduction in the best-corrected visual acuity (BCVA) of one or both eyes in the absence of obvious organic disease [1]. This reduction in BCVA is known to be due to an abnormal binocular experience originating during the critical period of visual system development, which may be caused by a misalignment of the eyes (strabismic amblyopia), a significant difference in the refractive error of the eyes (anisometropic amblyopia) or the presence of an ocular condition that prevents adequate visual stimulation (deprivation amblyopia) [2].

A wide range of large cohort and population-based studies have concluded that the global prevalence of amblyopia averages between 3 and 5%, making it the world’s leading cause of visual impairment in children and young adults [3, 4].

Current treatment of amblyopia emphasizes patching or penalizing the non-amblyopic eye to force the use of the affected eye, and although this is an effective method of improving visual acuity (VA), it has been associated with residual monocular and binocular deficits and a high risk of recurrence and non-compliance [5–7]. Furthermore, it has been argued that this monocular approach rarely results in the establishment of binocular function and is not considered valid in amblyopic patients who are beyond the critical period of visual system development [8, 9]. All these reasons have led to a substantial increase in research in the last decades on new treatment approaches that can satisfy both children and adults, with perceptual learning, video games and binocular treatment methods being the most relevant trends aimed at improving binocular fusion and reducing interocular suppression commonly present in amblyopia [10].

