### Pre-intervention (day 0)

Once the patient has been found to meet the eligibility criteria required for participation and the informed consent form has been signed, he/she will be seen in consultation prior to receiving the assigned intervention for a comprehensive eye examination including cycloplegic autorefraction and assessment of near and distance BCVA (monocular and binocular, logMAR scale, using the ETDRS chart), CSF (monocular, using the CSV-1000 test for spatial frequencies of 3, 6, 12 and 18 cycles per degree), binocular vision (using the Worth’s four-dot test), stereopsis (using the TNO stereoscopic test), fusional vergence (break and recovery), accommodative facility (measured as the number of changes made to achieve optimal focusing using a spherical flap of ±2 dioptres when the patient looks at a near optotype: VA 0.2 logMAR) and near convergence point (measured as the closest distance in centimetres in reference to the patient’s nasal root at which he/she is able to maintain single vision).

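### Adverse reactions are assessed only with a simulator-sickness questionnaire, and the fellow-eye acuity already collected is not identified as a safety outcome

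*Protocol article*

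**What the plan says.** The abstract of the protocol article gives safety, with efficacy, as what the trial is to evaluate. Hypothesis and aims lists safety among the further outcomes after the intervention.

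Only one measure is attached to harm. Under Post-intervention (day 90), "adverse reactions to therapy will be assessed using the standard and pediatric versions of the Simulator Sickness Questionnaire", with the version chosen by age.

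Acuity is measured eye by eye. The day 0 examination includes "assessment of near and distance BCVA (monocular and binocular, logMAR scale, using the ETDRS chart". The later visits repeat it: "After 1 and 2 months of therapy, the patient will be referred for re-evaluation of the visual outcome measures", then the same visual measures at day 90. Six months after that, patients are seen in routine care "for reassessment of the visual outcome measures considered in the study". The fellow eye is therefore measured by implication. BCVA is listed only as an efficacy outcome, and no outcome names the fellow eye.

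The Data analyses plan says that "descriptive analysis of all data will be provided, including means and SDs or medians for continuous variables". It adds proportions for categorical variables, and then the t-test, ANOVA, linear regression, rank tests and the chi-squared test.

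**The concern.** Both therapies shift the balance of visual input away from the fellow eye. The Background says: "Current treatment of amblyopia emphasizes patching or penalizing the non-amblyopic eye to force the use of the affected eye". Group B is prescribed 2 hours of this daily for 3 months. Group A sees stimuli at a different contrast in each eye, and the article describes dichoptic training as raising contrast for the amblyopic eye. The Background also lists, among the causes of amblyopia in the developmental period, "the presence of an ocular condition that prevents adequate visual stimulation (deprivation amblyopia". Children are enrolled from age 5. Reduced fellow-eye acuity is thus a plausible harm to look for in both arms, although the article does not say outright that either therapy causes it.

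The one named harm measure would not detect it. It also suits the patching arm poorly, since those children use no simulator, so the arms lack a well-matched common harm measure. At stake is the safety conclusion: drawn from the questionnaire alone, it could be favourable for either arm although a few children had lost lines in their better eye.

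**Working it through.** **1. Number of children per arm.** Inputs from Sampling: difference 0.15 logMAR, SD 0.195, alpha 0.05 (taken as two-sided), power 80%, loss to follow-up 10%.

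- n = 2 × [0.195 × (1.960 + 0.842) / 0.15]² = 26.5, rounded up to 27 per arm.
- 27 / 0.9 = 30 per arm.

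The stated 30 per group is reproduced. The point does not affect it. About 27 evaluable children per arm is the number used below.

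**2. What one child does to the arm mean.** The shift is loss / n. The standard error of the mean is 0.195 / √27 = 0.0375. The SD of 0.195 is the article's figure for the powered BCVA difference; applying it to the fellow eye is an assumption.

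| Loss in one child (logMAR) | Shift in mean of 27 | Shift / standard error |
|---|---|---|
| 0.1 | 0.004 | 0.10 |
| 0.2 | 0.007 | 0.20 |
| 0.3 | 0.011 | 0.30 |

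**3. Several children (all rates and changes assumed; positive means worse).** Three of 27 (11%) lose 0.20 logMAR, and the rest gain slightly through practice or maturation.

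- Others gain 0.02: (3 × 0.20 − 24 × 0.02) / 27 = (0.60 − 0.48) / 27 = +0.004, apparently no change.
- Others gain 0.03: (0.60 − 0.72) / 27 = −0.004, apparently a slight improvement.

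In both cases a count shows 3/27.

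**4. What a count can and cannot show.** The article gives no true rate, so a range is used. The chance of at least one case in 27 is 1 − (1 − p)^27.

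| Assumed true rate p | Chance of at least one case |
|---|---|
| 1% | 24% |
| 3% | 56% |
| 5% | 75% |
| 10% | 94% |

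With zero cases, the one-sided 95% upper limit is 1 − 0.05^(1/27) = 10.5%. A count with its interval therefore reveals individual losses and also shows how little an absence of cases proves at this sample size.

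**The case against.** The strongest objection is that this is a condensed article. Line-loss thresholds and harm tables commonly sit in the full protocol or analysis plan, and their absence here is no defect. That is right as far as it goes. But the article is not merely silent: it states how adverse reactions will be assessed, and the method it states does not measure acuity. That choice can be reviewed.

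Second, the Data analyses plan does not restrict fellow-eye acuity to a mean or median. Its list of summaries is introduced as examples, proportions and the chi-squared test are named, and the between-group tests could be applied to monocular acuity. This stands. A reader might infer that the fellow eye receives only a group average, that a child's loss would go unreported, or that the trial could not compare the arms on this eye. The text supports none of these. What remains is that the methods named for continuous data work at group level, and that nothing designates a per-child loss as a categorical safety outcome to which the proportions would apply.

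Third, the harm is inferred. The deprivation statement concerns an ocular condition, not 2 hours of daily patching, and total VR exposure is 9 hours. This also stands: the harm is plausible, not documented here.

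Fourth, the illustration in step 3 uses inputs chosen so that gains and losses nearly cancel. In its first case the SD of the changes is 0.22 × √(1/9 × 8/9) = 0.07, with skewness (7/9) / √(1/9 × 8/9) = 2.5, which the planned histogram and skewness checks could bring to the analyst's notice. Those checks serve to choose a test, however, not to report harms.

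**Conclusion.** The point holds as a gap in the stated harm assessment. Safety is an aim, adverse reactions are tied to one questionnaire that does not measure acuity, and the monocular acuity that could fill the gap is already planned but not identified as a safety outcome. A safety conclusion for either arm could therefore miss fellow-eye losses in a few children.

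The size cannot be fixed from the article, which gives no rate of fellow-eye loss. The firm figures are that a 0.2 logMAR loss in one child moves a 27-child mean by only 0.007, and that zero of 27 is compatible with a true rate up to 10.5% (one-sided 95%). The 3-of-27 case is illustrative. All of this assumes about 27 evaluable children per arm and monocular testing at each follow-up visit.

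A reader might also infer, because the primary outcome does not name the eye, that the two eyes could be averaged. Nothing in the article says so, and the point does not rest on it. Sample size and primary comparison are unaffected. The change is worth making before the data are analysed.

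**What to change.** - Name fellow-eye distance BCVA as a safety outcome in both arms, alongside the questionnaire.
- As the main summary, report per arm the number and proportion of children whose fellow-eye BCVA at day 90 is at least 0.2 logMAR worse than baseline, with exact confidence intervals and the between-arm difference.
- As supportive summaries, report the same at days 30 and 60, and for a worsening of at least 0.1 logMAR.
- Give the six-month reassessment descriptively where available, since it takes place in routine care outside the five study visits.
- If no case is seen, state the upper confidence limit next to any safety statement.

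The cost is a few lines of text and one extra table, with no new visits, tests or patients. The one-line count will include measurement noise, so some counted losses will not be real; this is why the two-line count leads. At this sample size the between-arm difference will be imprecise and should be read as descriptive. This is a reporting definition only and sets no treatment rule.
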